## Abstract

**Background:**

Cigarette smoking remains a leading cause of preventable illness and death, underscoring the need for effective evidence-based smoking cessation interventions. Nuumi, a novel smoking cessation program integrating a digital behavioral therapy and an electronic cigarette, may provide a solution.

**Objective:**

To investigate the initial efficacy, acceptability and psychological outcomes of an evidence-based smoking cessation intervention comprised of a mobile phone app and an electronic cigarette among adults who smoke and who are motivated to quit.

**Methods:**

A prospective 6-month single-arm mixed-methods pilot study will be conducted. Seventy adults who smoke and who are motivated to quit will be recruited via web-based advertisements and flyers. Participants receive access to an app and an electronic cigarette with pods containing nicotine for temporary use of at least 3 months. The electronic cigarette is coupled with the app via Bluetooth, allowing for tracking of patterns of use. The behavioral therapy leverages evidence-based content informed by cognitive behavioral therapy and mindfulness-informed principles. Web-based self-report surveys will be conducted at baseline, at 4 weeks, at 8 weeks, at 12 weeks, and at 24 weeks post-baseline. Semi-structured interviews will be conducted at baseline and at 12 weeks post-baseline. Primary outcomes will be self-reported 7-day point prevalence abstinence from smoking at 12 weeks and 24 weeks. Secondary outcomes will include other smoking cessation-related outcomes, psychological outcomes, and acceptability of the nuumi intervention. Descriptive analyses and within-group comparisons will be performed on the quantitative data, and content analyses will be performed on the qualitative data. Recruitment for this study started in October 2023.

**Discussion:**

As tobacco smoking is a leading cause of preventable morbidity and mortality, this research addresses one of the largest health burdens of our time. The results will provide insights into the initial efficacy, acceptability, and psychological outcomes of a novel mobile health intervention for smoking cessation. If successful, this pilot may generate an effective intervention supporting adults who smoke to quit smoking. The results will inform feasibility of a future randomized controlled trial.

*Trial Registration* German Clinical Trials Register DRKS00032652, registered 09/15/2023, https://drks.de/search/de/trial/DRKS00032652.

## Introduction

Worldwide, tobacco use constitutes a leading cause of preventable illness and death [1]. A variety of evidence-based psychological and pharmacological interventions are available to support cessation, including brief behavioral counseling, telephone counseling, behavioral therapy in one-on-one or group settings, nicotine replacement therapy (NRT), or pharmacotherapy such as varenicline, bupropion, or cytisine [2]. However, these treatments are rarely utilized by adults who smoke to support cessation [3], and even when used, long-term abstinence rates tend to be relatively low, often falling below 15% at 6 to 12 months after the intervention [4]. Hence, new and effective treatment approaches for adults who smoke and who are willing to quit smoking are needed.

A drawback of conventional treatments such as NRT products is that, while they may effectively replace nicotine intake, they do not fully address the sensory, behavioral, and social characteristics of smoking; including activities like holding a cigarette, taking puffs, deriving pleasure from smoking, or feeling part of a social group while using them [5]. A method that may circumvent these limitations is the use of electronic cigarettes (ECs).

### Electronic cigarettes for smoking cessation

ECs constitute a novel and diverse product class of electronic devices comprised of a reservoir holding a liquid solution, a power source (e.g. battery), and a heating element [6]. The liquid solution contains solvents such as vegetable glycerin and/or propylene glycol, flavorings (e.g. tobacco, menthol) and may contain nicotine [6]. Although not officially approved as a smoking cessation aid in most countries, like Germany [2] or the U.S. [7], ECs are the most popular smoking cessation tool in Germany [3], and in the U.S., almost half of adults who smoke and want to quit indicate they had tried ECs [8].

The use of ECs has been linked to significantly greater smoking abstinence rates relative to non-supported quitting attempts [3], and there is high-certainty evidence available that nicotine-containing ECs support smoking cessation more effectively than NRT, and moderate certainty evidence that they increase quit rates compared to ECs without nicotine [5, 9]. The relative effectiveness of ECs may be partially explained by the higher reduction in withdrawal symptoms relative to NRT products [10]. The degree to which ECs can effectively suppress nicotine withdrawal symptoms varies across devices [11, 12], and nicotine delivery is dependent on various factors, including device power [13], nicotine concentration [14], and user experience [12]. ECs deliver some of the sensory and motoric components of cigarette smoking, e.g. hand-to-mouth movement and “throat hit” [5, 15]. Therefore, ECs may have the potential to alleviate undesirable nicotine withdrawal symptoms while addressing both the behavioral aspects, rituals and sensations associated with smoking [5]. In fact, even non-nicotine-containing ECs have been linked to suppression of some withdrawal symptoms [12].

Another advantage of ECs is that they allow for individual tailoring of nicotine doses [10] and hence may be used to reduce nicotine over time. In combustible tobacco cigarettes, reducing nicotine content has been linked to a reduction in the relative reinforcing effects of smoking, a key marker of dependence potential [16].

However, although evidence suggests that ECs are likely to be less harmful than combustible cigarettes, they are not without risk, and concerns remain regarding the long-term safety of their usage [17]. While ECs may serve as an effective smoking cessation tool, meta-analysis data shows that approximately 70% of individuals who underwent EC-supported smoking cessation report ongoing EC use at six months or longer [18]. Because the long-term health consequences of ECs use are unknown, EC-supported smoking cessation efforts should include steps to wean individuals who had previously smoked off ECs once smoking cessation has been attained.

In summary, ECs can serve as effective smoking cessation tools by providing individuals with nicotine to suppress withdrawal symptoms. However, individuals undergoing a smoking cessation attempt also suffer from increased affective symptoms such as depressive or anxious mood, irritability, and restlessness [19–21], and factors such as an encounter with other adults who smoke or experiencing stress may further exacerbate the risk of relapse [22, 23]. Thus, to provide adults who smoke with a successful smoking cessation intervention, a program should include components that address the psychological mechanisms of addiction in addition to physical symptoms.

### Behavioral interventions for smoking cessation

Evidence suggests smoking cessation efforts are more effective when behavioral support is offered in addition to NRT interventions [24, 25]. Effective behavioral treatments include brief cessation counseling, telephone support, text messaging interventions, mobile application, or webpages, and face-to-face individual or group-based cognitive behavioral therapy (CBT) [26] with the latter having been shown to be more effective than brief advice, self-help materials, or counseling [26].

CBT is a psychological treatment approach that aims to help individuals quit smoking by modifying thoughts, beliefs, and behaviors associated with smoking [27]. CBT-based interventions often target problem solving and coping skills, teaching strategies like cognitive restructuring of maladaptive thoughts [27–29]. As a further development of CBT, mindfulness-informed interventions (MIIs) have emerged within the so-called third-wave generation of CBT treatments [30, 31]. In MIIs, conventional CBT methods are enriched with mindfulness- and acceptance-based strategies as well as metacognitive and meditative components [2]. Mindfulness typically involves intentionally directing one’s attention toward physical sensations, emotions, and thoughts to cultivate a heightened awareness and foster a nonjudgmental acceptance of these inner experiences [32]. Mindfulness training usually includes training of attention regulation, body awareness, emotion regulation, and self-awareness among other skills [33, 34]. In smoking cessation, mindfulness training teaches individuals the skill to act as an observer of one’s own affective state and cessation-related cravings instead of reacting by resorting to smoking [35]. While a recent Cochrane review was unable to detect clear benefits of mindfulness training for smoking cessation when compared with other smoking cessation treatment or no treatment [36], some literature has pointed out that adding a mindfulness component may increase the likelihood of quitting smoking [37]. Importantly, mindfulness seems to act on factors related to smoking and may therefore indirectly impact smoking abstinence. For example, mindfulness training may aid in reducing the number of cigarettes smoked per day [38], weaken the link between cigarette cravings and smoking [39, 40], and enhance the self-efficacy of adults who smoke for managing negative emotions without using cigarettes [41].

However, while adding psychological components to smoking cessation interventions can generally increase intervention effectiveness, in-person counselling is costly and is difficult to access for some due to limited financial resources and time. While in-person interventions may not present a feasible and scalable treatment for all adults who smoke and are willing to quit, digital behavioral therapies provide an easily accessible alternative. Mobile health (mHealth) interventions like smartphone apps offer numerous advantages over traditional in-person behavioral smoking cessation support, such as improved accessibility and availability, real-time support, personalization of features, cost-effectiveness, and scalability [42–44].

Currently, there are few high-quality studies available examining the effectiveness of smartphone apps for smoking cessation [45], and the content of many currently available app-based programs is only marginally consistent with evidence-based treatment guidelines [44, 46]. However, in principle, digital therapeutic interventions offer opportunities for intensive therapeutic programs and recent studies suggest that such interventions can effectively support smoking cessation [42, 45, 47, 48]. Importantly, a growing body of literature highlights the effectiveness of digital CBT-based programs for smoking cessation [42, 49], and MIIs have also shown initial efficacy when delivered via mHealth [50].

The aforementioned findings highlight mHealth applications as a promising tool for providing effective behavioral smoking cessation interventions. However, while an increasing number of smoking cessation apps are tailored to be administered alongside NRT, to our knowledge, there is no mobile application available supporting adults who smoke and want to quit by using ECs.

Considering the findings that some ECs can support smoking cessation more effectively than NRT, and smartphone apps provide the opportunity to offer behavioral support to adults who smoke and are willing to quit, Sanos Group GmbH (Berlin, Germany) developed an evidence-based smoking cessation program featuring an integrated EC and app-based behavioral therapy, *nuumi*. This study will be the first trial to evaluate the intervention.

### Objectives

The primary objective of this study is to assess initial efficacy of the nuumi program, defined as self-reported 7-day point prevalence abstinence from smoking at 12 weeks and 24 weeks after initiation. Secondary objectives are to examine within-group changes in smoking cessation-related and psychological outcomes, including urges to smoke, perceived stress, mindfulness, self-efficacy to abstain from smoking, subjective health, and life satisfaction. A further secondary objective is to investigate the acceptability of the nuumi program, indexed by perceived usefulness in quitting smoking, user satisfaction, comprehensibility of the content, and usability of the app. The objective of the qualitative interviews is to explore the perspectives of adults who smoke on quitting using electronic cigarettes and apps before the intervention, and their perspective about the intervention after completion. Overall objective of this single-arm trial is to pilot and optimize procedures of a subsequent RCT, in which the nuumi intervention will be compared to a treatment-as-usual (TAU) control group.

## Methods

### Study design and setting

This study is a prospective 6-month, single-arm mixed-methods pilot study designed to evaluate smoking cessation outcomes, acceptability, and psychological outcomes of the mHealth intervention nuumi. Data will be collected in Germany.

### Participants

Interested individuals are screened for eligibility by completing a brief online questionnaire. Eligible participants are aged 18–65 years, report having smoked at least 5 cigarettes per day (CPD) for at least 12 months, are motivated to stop smoking (Motivation To Stop Scale (MTSS; [51]) > 4 points), have daily access to their own smartphone (iOS 15/Android 11 or more recent), reside in Germany, have access to a personal email account, and report being able to read and write in German.

Ineligibility criteria include self-reported current or planned pregnancy, breastfeeding, a self-reported allergy to vegetable glycerin or propylene glycol, drug and/or alcohol dependence, severe psychiatric or physical illness, a disease or medication associated with a contraindication to the use of EC, and medication that could affect the outcomes of the study (bupropion/ nortriptyline/ varenicline/ cytisine/ clonidine/ antidepressants). Exclusion criteria also include surgery (with anesthesia) in the last 6 weeks, participation in any other smoking cessation program, current use of EC/tobacco heaters/alternative tobacco products/NRT for more than 5 days during the last 30 days, and the inability to consent.

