#### Primary and secondary outcomes

##### Primary outcome

The primary outcome will be self-reported 7-day point prevalence abstinence from smoking (PPA) at t_3_ and t_4_, operationalized as not having smoked any cigarettes, not even a single puff, in the last 7 days [62].

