##### Adherence and engagement

Adherence is operationalized as (1) self-reported use of the EC (current use and number of days of use), and (2) self-reported engagement with the app (number of daily/weekly uses, number of modules completed, minutes meditated). Participants will be asked whether they participate in any other smoking cessation program in each survey from t_0_ onwards.

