##### Primary and secondary outcomes

For the primary outcome, 7-day PPA at t_3_ and t_4_, number and percentage of participants self-reporting abstinence will be reported. For the secondary outcomes, measures of frequency and percentages will be reported for 30-days PPA, repeated PPA and continuous PPA, and measures of central tendency will be reported for CPD and urges to smoke. Paired t-tests will be conducted to assess changes in CPD and urges to smoke from t_0_ to t_3_ and from t_0_ to t_4_. Mean and SD will be reported for perceived stress, mindfulness, smoking self-efficacy, subjective health and life satisfaction, and paired t-tests will be conducted to assess within-subject changes in these variables. Acceptability outcomes will be reported descriptively.

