##### Other variables

Frequency measures and percentages will be reported for method(s) of previous quit attempts, use of alternative tobacco products and ECs, participation in other smoking cessation programs, NRT use, and EC dependence. Mean and SD will be calculated for years of smoking, motivation to quit, number of previous quit attempts, and withdrawal symptoms. To assess adherence and engagement, frequencies and percentages of current EC use, and number of days of use will be reported. Mean and SD for engagement with the app will be calculated. Further, frequencies and percentages will be reported for the subjective evaluation of the EC, side effects, and adverse events.

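### Abstinence reached with other cessation aids after entry counts in full towards nuumi's efficacy, and cessation drugs barred at entry have no follow-up row in the schedule

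*Protocol article*

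**What the plan says.** **Entry.** The Participants section bars "medication that could affect the outcomes of the study", naming bupropion, nortriptyline, varenicline, cytisine, clonidine and antidepressants. The same section bars "participation in any other smoking cessation program, current use of EC/tobacco heaters/alternative tobacco products/NRT for more than 5 days during the last 30 days". Only the drug list carries a stated reason. NRT and the other products bar entry only above the 5-day threshold.

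**Efficacy.** The Objectives section sets the primary aim as to "assess initial efficacy of the nuumi program, defined as self-reported 7-day point prevalence abstinence from smoking at 12 weeks and 24 weeks after initiation". The Primary outcome section has abstinence "operationalized as not having smoked any cigarettes, not even a single puff, in the last 7 days". Neither places a condition on other cessation aids.

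**Analysis.** Under Statistical methods, Primary and secondary outcomes, the "number and percentage of participants self-reporting abstinence will be reported". The intention-to-treat rule treats only a missing survey as a failure, and the complete-case set depends only on survey completion.

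**Data on other aids.** Under Adherence and engagement, "Participants will be asked whether they participate in any other smoking cessation program in each survey". Table 2 in Appendix A also schedules NRT use, EC use and alternative tobacco products at every survey. Under Statistical methods, Other variables, the plan is to give frequencies and percentages for "participation in other smoking cessation programs, NRT use, and EC dependence". Table 2 has no row for the drugs named in the entry criteria.

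**The concern.** The protocol names one influence on the outcome, cessation medication, and removes it at entry. After entry it neither restricts that influence, nor schedules its recording, nor allows for it in the efficacy figure. Someone who stops responding to nuumi, starts one of the listed drugs and is abstinent at 24 weeks is counted as a nuumi success. The same holds for NRT or another program, although those data will at least be in hand.

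A randomised comparison would let co-intervention be compared between arms. Here there is one arm, and the abstinence rate itself is labelled efficacy of the program. Strengths and limitations goes on to offer the descriptive results as a preliminary indication of how nuumi compares with other cessation interventions. At stake is what may be said about nuumi from the t3 and t4 rates. No error rate or power is affected.

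**Working it through.** The protocol states no figure that depends on this point. The sample size of 70 is expressly not from a formal calculation, so there is nothing to reproduce. The check is first textual, then a sizing under assumptions.

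**Places set side by side**

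| Aid | Barred at entry | Scheduled at t1 to t4 (Table 2) | Use in the primary analysis |
|---|---|---|---|
| Listed cessation drugs | Yes, reason stated | No row | None |
| Other cessation program | Yes, no reason stated | Yes | None; frequencies only |
| NRT | More than 5 of last 30 days, no reason stated | Yes | None; frequencies only |
| Other ECs, alternative tobacco products | More than 5 of last 30 days, no reason stated | Yes, as EC use and alternative products | None; frequencies only |

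Three things follow.

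1. The primary outcome depends on not smoking and on nothing else, so abstinence with any other aid is a success.
2. For programs and NRT, a second figure can largely be built from planned data. One caution: Smoking behavior-related variables lists *current* program participation and *current* NRT use. If the surveys ask it that way, an aid taken up and dropped in the 12 weeks between t3 and t4 could be missed.
3. For the drugs, no analysis plan can recover the information later unless an item is added.

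**Size under assumptions**

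Inputs: n = 70 (Sample size section). The number abstinent, x, and the share of abstainers who used another aid, s, are not in the document; both are assumed.

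Formulas: k = s × x, rounded; planned rate = x/70; rate without other aids = (x − k)/70; difference = k/70.

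- x = 18: planned rate 18/70 = 25.7%.
  - s = 10%: 1.8, so k = 2; 16/70 = 22.9%; difference 2/70 = 2.9 points.
  - s = 30%: 5.4, so k = 5; 13/70 = 18.6%; difference 5/70 = 7.1 points.

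Wider range:

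| x (rate) | s = 10% | s = 20% | s = 30% |
|---|---|---|---|
| 14 (20.0%) | 13/70 = 18.6% | 11/70 = 15.7% | 10/70 = 14.3% |
| 21 (30.0%) | 19/70 = 27.1% | 17/70 = 24.3% | 15/70 = 21.4% |
| 28 (40.0%) | 25/70 = 35.7% | 22/70 = 31.4% | 20/70 = 28.6% |

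The difference runs from 1/70 = 1.4 points to 8/70 = 11.4 points.

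These are ceilings. If a fraction f of the k co-users would have been abstinent anyway, the excess is (1 − f) × k/70. With k = 5 and f = 0.5 it is 2.5/70 = 3.6 points; with f = 1 it is zero.

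For scale, the Wilson 95% interval for 21/70 is 20.5% to 41.5%. The possible shift is smaller than the sampling uncertainty, but it is systematic and the interval does not cover it.

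**The case against.** The strongest reply is that nothing here contradicts anything else. Entry criteria fix the population at baseline. Counting abstinence whatever happens afterwards is a coherent choice and sits well with an intention-to-treat rule. Nowhere does the protocol promise a rate for nuumi alone. This stands, and it is why the planned rate should be kept.

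Second, a sensitivity analysis is something an article may leave to the analysis plan. That is fair for the extra figure taken alone. It does not dispose of the point, because the article itself fixes the efficacy definition, the failure rule, the complete-case set, the use made of the co-use data and the assessment schedule.

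Third, the study is described as exploratory and mainly descriptive, it admits limited internal validity without a control group, and its overall aim is to prepare an RCT against treatment as usual. This also stands and limits the weight of the point. Use of other aids during follow-up is not, however, among the limitations listed.

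Fourth, the document gives no reason to expect heavy co-use. The Introduction says that conventional treatments are rarely used. The true excess could be near zero.

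Several stronger readings are tempting, and the text does not support them:

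- *All these aids were barred because they affect the outcome.* That reason is written only for the medication list. For programs, NRT and the other products it is an inference, and lighter NRT use is tolerated at entry.
- *The bias is greatest at 24 weeks because the pods run out.* Three months is the minimum supply and app access is unlimited. Nothing shows that participants change aids then.
- *The adjusted rate can be set against the long-term rates below 15% in the Introduction.* Those are at 6 to 12 months after the intervention, while t4 is 24 weeks after baseline, so the two are not like for like.

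**Conclusion.** The point holds as one of interpretation. As written, the t3 and t4 rates credited to nuumi include abstinence reached with any other aid, no comparator offsets this, and use of the listed drugs during follow-up could not be separated out from the scheduled data. The rates may therefore overstate what is attributable to nuumi.

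By how much is unknown. With 18/70 abstinent and 10% to 30% of them using another aid, the ceiling is about 3 to 7 points; across 20% to 40% abstinence it is about 1 to 11. Every one of these figures rests on assumed rates and on the extreme case that no co-user would have quit otherwise. They should not be read as an estimate of actual overstatement. The point deserves action because the remedy is small and bears directly on how the primary result is worded.

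**What to change.** 1. Keep the planned 7-day abstinence rate as the primary figure at t3 and t4, and label it as abstinence regardless of other cessation aids.
2. Beside it, as a sensitivity analysis, report the rate with certain abstainers counted as not abstinent with nuumi alone. These are abstainers who reported a listed cessation drug, another cessation program, or use of NRT, a non-study EC or an alternative tobacco product above a pre-stated threshold. The entry criterion's own more than 5 days in 30 would serve; treating any use since baseline as failure would be stricter than the entry rule itself. The surveys must distinguish the study EC from others and give days of use. Describe the result as a conservative lower figure.
3. Add one yes/no item on the listed drugs, covering the time since the last survey, to the surveys still to be completed.
4. Word efficacy statements on both figures.

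**Cost.** One survey item, one extra table line and a second figure that will look less favourable. Recruitment began in October 2023 and completion was anticipated for June 2024, so drug data will be incomplete for participants already past earlier surveys. That gap should be reported as a limitation.
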